Our team has previously conducted two systematic reviews to synthesise the existing evidence of self-managed non-pharmacological interventions for BCSs [34] and CVDs [35]. The reviews identified common non-pharmacological interventions for BCSs and CVDs, which could guide the selection and development of an evidence-based non-pharmacological intervention programme for BCSs with CVDs in this research project. Managing two complex health conditions, BC and CVD simultaneously presents distinct challenges such as clinical and system-level challenges that may influence how patients respond to or benefit from self-managed non-pharmacological interventions. Clinical challenges such as shared modifiable and non-modifiable risk factors, cardiotoxic effects of cancer treatments, and poor cancer outcomes due to CVD, and system-level challenges such as poor integration of cardio-oncology services, lack of coordination between specialties, absence of a shared care model and limited awareness among clinicians about cardiotoxicity complicate the long-term surveillance of BCSs [4,28,36,37]. Considering these challenges and the elevated risk for CVDs, this highlights an urgent need for tailored, evidence-based self-management interventions delivered within primary healthcare.

This research project was thus proposed to develop a nurse-led and GP-supported self-management (NGPS) intervention for BCSs with CVDs and evaluate its feasibility and potential effects in primary care settings with the following specific objectives: (1) To develop an evidence based NGPS intervention protocol that is tailored to the needs of BCS with CVDs; (2) To examine the feasibility, acceptability, and safety of the NGPS intervention in BCS with CVDs; (3) To test the preliminary effects of the NGPS intervention on cardiovascular health outcomes, such as physiological outcomes, behavioural outcomes including dietary intake, physical activities and smoking, psychosocial outcomes including self-efficacy, QoL, anxiety and depression, and healthcare usage, in BCS with CVDs; (4) To explore the experiences of patients and healthcare professionals who participate in this pilot study and to identify any barriers and facilitators in the implementation of the NGPS intervention in Australian primary care settings; and (5) To refine the NGPS protocol based on the results of this pilot trial and the qualitative process evaluation.

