Potential participants will be identified and approached in collaboration with the primary care centres and the healthcare professionals. The participants will be informed of the study by the treating doctor or the centre by using flyers or through emails sent by the centre reception. The healthcare professionals at the centre will be introduced to the study through meetings, presentations or brochures to help with the recruitment and to distribute the participant information sheet. The interested participants will contact the primary researcher. Prior to recruitment, potential participants will be screened for eligibility, and informed consent will be obtained from eligible participants after explaining the study’s purpose, procedures, and risks. Participants will be advised to continue receiving usual care from their medical centre during the study.

The planned data collection will be taking place at three points during the study: at the beginning of the study before the intervention (T1). At week four immediately after the NGPS intervention (T2) and at week 12, which is eight weeks post-intervention (T3). The eight-week follow-up is based on previous research suggesting that it typically takes around eight weeks for individuals to change a habit or behaviour [62]. The interventions will be carried out through a combination of telehealth and in-person consultations, with alternating durations depending on the session type.

A qualitative process evaluation will be conducted at the end of the intervention, at week four by using semi-structured interviews. All the participants will be invited to participate in the qualitative interviews.

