The secondary outcomes will measure the physiological outcomes, which include weight, BMI, blood pressure and heart rate. The secondary outcomes will also evaluate the clinical outcomes, the preliminary effects of the NGPS intervention on various measures, behavioural outcomes, which include dietary outcomes, physical activity and smoking status; psychological outcomes which include self-efficacy, QoL, and anxiety and depression; and lastly healthcare usage.

The dietary outcome will be measured using a 15-item Food Frequency Questionnaire (short 15-item FFQ), which has been tested in female patients and widely used in cardiac patients to screen poor dietary patterns and has an overall good agreement with the diet history [63,64].The International Physical Activity Questionnaire-Short Form (IPAQ-SF) is a nine-item self-report tool and is a well-validated tool tested in Australian adults which will be used to assess physical activity, which has good reliability and validity when used in BCS [65,66].The smoking status will be assessed using a self-reported questionnaire.Psychological outcomes include self-efficacy, which will be measured using the General Self-Efficacy Scale (GSES) [67]. The GSES is a 10-item psychometric instrument to measure the participants’ ability to cope with various challenging situations, has good reliability and validity across a range of populations and is recommended for use in pilot studies [67].The QoL will be measured using the Functional Assessment of Cancer Therapy-Breast (FACT-B), a 37-item tool targeted for BC patients, which showed satisfactory reliability and validity [68].The anxiety and depression will be measured using a 14-item Hospital Anxiety and Depression Scale (HADS), which has been widely adopted in cancer patients and in primary care settings and noted to have satisfactory psychometric properties [69].The healthcare usage will be measured using an investigator-created logbook by measuring the number of hospital visits or GP visits for cardiovascular conditions during the phone calls.

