#### 2.2.2. Data Analysis of the Pilot Study

Data will be analysed using descriptive and exploratory inferential statistics using SPSS 26.0 with the intention of feasibility assessment and not for formal hypothesis testing [70]. In a single-group pre-post-test study, the characteristics of the sample will be summarised using descriptive statistics such as frequency counts, percentages, means, and standard deviations. The descriptive data analysis can give an overview of the sample’s age, gender, ethnicity, education level, income, breast cancer treatments, and other demographic variables.

The feasibility outcomes of the study such as recruitment, follow-up assessments, and questionnaire/intervention acceptability will be determined using descriptive data [71]. Mean and standard deviation will be used to analyse interval and ratio data, such as the time taken for participant recruitment and the average time and frequency of physical activity [71]. The acceptability of the questionnaires will be determined by calculating the proportion of missing data [71]. The feedback on the intervention is measured by assessing the participants’ satisfaction scores. Any adverse events related to physical activity, such as musculoskeletal aches and pain, dizziness, and falls, will be presented as the absolute number of events and the total percentage.

Secondary clinical and behavioural outcomes will be presented descriptively at each assessment point to evaluate the feasibility outcomes for future randomization [70]. Changes over time will be explored using non-parametric methods, given the small sample size and single-group pre–post design [71,72]. The Friedman test will be conducted for continuous variables to correlate the data at three different time points [73]. Cochran’s Q test will be utilised for categorical variables to assess changes in proportions between the pre-test and post-test assessments [74]. These analyses will be exploratory only and will not be interpreted as formal hypothesis tests. Analyses will be conducted using available data from participants who complete each assessment. The extent and reasons for missing data will be reported. Participant attrition will be monitored throughout the study, and differences between completers and non-completers will be examined to evaluate potential attrition bias. No imputation of missing data is planned due to the small sample size and feasibility focus of this study.

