W1 Initial nurse-led consultation	Format: in-person Time: 15–30 min Health professionals: nurse, and involve allied health professionals if needed Patients: patient and caregiver	Assess the breast cancer survivors’ knowledge of their cardiac conditions and breast cancer, evaluate health literacy, access to resources and motivation to manage their health condition by using the COM-B model. Using the COM-B model, identify the patients’ needs, preferences, and goals and the factors influencing self-management by evaluating their capability, opportunity and motivation to manage their health effectively. Select suitable intervention strategies from the “intervention strategy pool” and develop personalised care plans based on identified factors and a multidisciplinary approach using the COM-B model.
W1 Self-management session	In-person 45–60 min Nurse, patient, and caregiver Involve GP and allied health professionals if needed	Further detail the overall care plan and teach and/or demonstrate the selected suitable intervention strategies to support the behaviour change in patients and evaluate patients to ensure they have mastered the skills for optimal outcomes. Enhance the patient’s capability by providing an education booklet that promotes explicit understanding and engagement in self-management behaviours.
W2 Telehealth with nurse	Telehealth or in-person 15–30 min Nurse and patient	Nurse-led weekly telehealth support sessions using the COM-B model Monitor progress and the appropriateness of the implemented intervention strategies such as frequency and duration to ensure they effectively support the behaviour change. Provide guidance and support to enhance the patient’s capability. Reassess and adjust the care plan based on ongoing assessments to ensure optimal outcomes. Reinforce behaviour change techniques to enhance motivation. Instruct patients to report any healthcare usage during the intervention to maintain accurate monitoring. Encourage patients to ask questions and seek clarification to improve understanding and engagement.

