W3 Telehealth with nurse	Telehealth or in-person 15–30 min nurse, patient, and caregiver	Nurse-consultation Medical evaluation. Address any medical concerns via coordination with the multidisciplinary team (including GP and allied health if needed). Review and update the care plan as needed. Check whether all the intervention strategies were correctly implemented. Nurse-led weekly telehealth support sessions (content the same as week 2).
W4 Telehealth with nurse	Telehealth or in-person 15–30 min Nurse, patient, and caregiver	Nurse-led weekly telehealth support sessions using the COM-B model (contents the same as week 2)

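### Healthcare usage is a pre-post outcome, but the collection described gives no value before the intervention and names no contact covering weeks 5 to 12

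*Protocol article*

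**What the plan says.** The Introduction lists the outcomes on which objective 3 will test preliminary effects. The list ends with "anxiety and depression, and healthcare usage, in BCS with CVDs".

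Section 2.2.1, under secondary outcomes, says that an investigator-created logbook will capture usage "by measuring the number of hospital visits or GP visits for cardiovascular conditions during the phone calls". It states no look-back period, count window or rate.

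Table 3 says when patients are told to report. The week 2 session includes this item: "Instruct patients to report any healthcare usage during the intervention to maintain accurate monitoring". Weeks 3 and 4 repeat the week 2 content. Both week 1 sessions are in person, and the table ends at week 4.

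Section 2.2, Study procedure, sets T1 "at the beginning of the study before the intervention (T1"), T2 at week 4, and T3 "at week 12, which is eight weeks post-intervention (T3").

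Section 2.2.2 presents secondary clinical and behavioural outcomes at each assessment point. For change over time it says: "The Friedman test will be conducted for continuous variables to correlate the data at three different time points". It labels these analyses exploratory, uses available data and plans no imputation.

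**The concern.** A pre-post outcome needs a value from before the intervention that was obtained in the same way as the later values. Here the only described source is a set of calls that begin after T1, and the reporting instruction covers the intervention period only. An analysis plan written later cannot repair this, because it cannot recover a baseline that was never collected.

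The second difficulty is the spacing of the assessments. A visit count grows with the time over which it is taken. Weight, blood pressure and questionnaire scores do not, so a schedule of week 0, week 4 and week 12 suits them. A raw count since the last assessment would cover twice as long at T3 as at T2.

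What is at stake is one component of objective 3 and the usefulness of this item for planning the later large-scale trial. A descriptive table of counts by time point would carry the same distortion, with or without a p-value.

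**Working it through.** **1. Collection set against analysis.**

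| Time point | Period before it | Described source of a visit count |
|---|---|---|
| T1 (before intervention) | none stated | none: calls have not started, week 1 is in person |
| T2 (week 4) | weeks 1–4 | nurse sessions in weeks 2, 3 and 4 |
| T3 (week 12) | weeks 5–12 | none described: Table 3 ends at week 4 |

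The article does not define the phone calls. I read them as the Table 3 sessions, the only scheduled patient contacts it describes in that period. On that reading one of the three cells has a source. A complete three-point comparison needs all three.

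**2. The plan's own figure.** The article gives no figure for healthcare usage. Its sample size reproduces: 12 / (1 − 0.20) = 15. I use n = 12 evaluable and n = 15 recruited below.

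**3. What raw counts would do.** Let r be a constant weekly visit rate. Suppose counts run from one assessment to the next (an inference from the schedule). The expected count is 4r at T2 and 8r at T3, a ratio of 2 with no change in behaviour. At 1 visit per month, r = 1/4.345 = 0.230, so the expected counts are 4 × 0.230 = 0.92 and 8 × 0.230 = 1.84.

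**4. How often a test would flag it.** Assumptions: Poisson counts at a constant rate, Friedman test at nominal 0.05 (the article states no level), 2,000 runs per setting. Windows are weeks counted for T1, T2 and T3. Entries are the share of runs with p < 0.05 at n = 12.

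| Visits per month (assumed) | Raw (4, 4, 8) | Per week (4, 4, 8) | Equal (4, 4, 4) |
|---|---|---|---|
| 0.25 | 13% | 7% | 5% |
| 0.5 | 23% | 7% | 4% |
| 1 | 41% | 6% | 4% |
| 2 | 66% | 5% | 4% |

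At n = 15 the raw (4, 4, 8) column runs from 15% to 76%. These columns suppose a 4-week look-back at T1, which the article does not provide. They show that adding a baseline alone does not cure the problem. Equal windows bring the share back to the nominal level, and rates bring it close (4% to 9% over both sample sizes).

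**5. T1 entered as zero.** With windows (0, 4, 8) and n = 12, the share is 47%, 92%, 99.9% and 100% at the same four rates.

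**6. Dependence on the rate.** At 0.25 visits per 4 weeks a person makes 0.25 × 13 = 3.25 cardiovascular visits a year. At 0.1 and 0.05 per 4 weeks (1.3 and 0.65 a year), zero at T1 gives about 16–17% and 7%. A 4-week look-back with an 8-week T3 count gives about 8% and 4%.

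**The case against.** **The windows are not in the article.** The schedule gives assessment times, not count windows, so the 4- and 8-week periods are inferred. This stands, and step 3 is conditional on it. It also cannot be combined freely with the gap after week 4: if nothing is collected then, there is no 8-week count. These are two alternative failures. On the described route T3 has no source. If the week 12 assessment does collect visits, its window must be matched to the others.

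**A reader might infer that the planned Friedman test will show a false rise, almost surely at common visit rates.** The documents do not support that. The test is not assigned to healthcare usage by name. A T1 value that was not collected is missing, not zero, and no imputation is planned, so a three-point test could not be run at all. The figures in step 5 therefore describe a possible misuse, not the plan. The visit rate is also unknown, and at low rates the effect almost disappears.

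**A reader might also infer that visits triggered by the intervention will inflate the count.** Table 3 involves the GP only if needed and coordinates medical concerns in week 3. Nothing says that such contacts are logged as cardiovascular visits. This is a possibility to guard against, not a shown error.

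**An article leaves logbook layout and recall periods to other documents.** This is fair for the wording of the item and for the use of rates. It does not answer the main point, because the article does state a collection route and that route begins after baseline.

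**The analysis is exploratory.** This is true and it limits the consequence. It does not make the counts comparable.

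**Conclusion.** The point holds in a limited form. As described, healthcare usage has no pre-intervention value and no stated source for weeks 5 to 12, so the comparison over time that objective 3 implies cannot be made. This rests on the article's text and on reading the phone calls as the Table 3 sessions.

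If raw counts since the previous assessment were used, the expected count would double from T2 to T3 at a constant rate. The chance of a nominally significant result would range from near nominal to about two in three at n = 12, depending on a visit rate that the article does not give. That part is conditional on inferred windows, Poisson counts and an assumed 0.05 level.

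The outcome is secondary and the analysis exploratory, so the feasibility conclusions are not at risk. It should still be settled before enrolment, since prospective data collection cannot be redone.

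**What to change.** - At T1, T2 and T3, ask the same question on cardiovascular GP and hospital visits over the same fixed look-back, for example the previous 4 weeks. Alternatively, record the length of each window and express usage as visits per person per 4 weeks.
- Note contacts arranged by the NGPS team separately, so that they can be shown apart.
- Report the outcome descriptively, as rates with confidence intervals, and state that raw counts do not enter the Friedman test.

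The cost is one extra self-report item at T1 and T3, with recall error, and the ethics variation that section 2.2.3 requires for protocol changes. No extra visit is needed, because T1 and T3 are already scheduled, and no extraction of practice records is required. A 4-week look-back at T3 covers weeks 9 to 12 and leaves weeks 5 to 8 uncounted. If that period matters, use the rate option with an 8-week window at T3.

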#### 2.2.1. Outcomes and Measurements

The study will employ a demographic data sheet that has been specifically developed by the research team to gather information on the socio-demographic characteristics of the patients, such as age, height, race/ethnicity, as well as their medical history, such as date of BC and CVD diagnosis, the current stage of BC, the type and date of BC and CVD treatment.

(1)Primary outcomes

The primary outcomes will be the feasibility, acceptability and safety outcomes. The feasibility outcome will measure the feasibility of the questionnaires, recruitment and the intervention delivery. The acceptability of the intervention will be assessed by assessing the acceptability among the participants. The safety of the intervention will be measured by the safe delivery of the intervention. The primary outcome will also measure the recruitment, retention, and dropout and will be evaluated as the fundamental aim.

The recruitment rate is the percentage of eligible participants who consented to participate in the study.The retention rate will measure the percentage of participants who remain in the study throughout the entire study period, from enrolment to follow-up (week 12).The dropout rate will be calculated based on the percentage of participants withdrawn from the study after enrolment.The feasibility of the questionnaires will be assessed by measuring the percentage of missing responses for each item and the entire scale.The feasibility of the recruitment will be assessed by measuring the number of weeks or months needed to achieve the target number of sample size.The adherence rate to the NGPS protocol will measure the percentage of participants who followed the interventions as intended. This will measure the feasibility and acceptability of the study intervention.The safety of the intervention includes discomfort or adverse effects related to NGPS intervention by keeping a daily logbook and reporting via telephone or face-to-face.Acceptability will assess the participant’s satisfaction, benefits received and obstacles faced using an investigator-created questionnaire.

(2)Secondary outcomes

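### Healthcare usage has two unreconciled scopes, and because safety covers only related events, a non-cardiovascular visit judged unrelated is reported nowhere

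*Protocol article*

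**What the plan says.** All references are to the protocol article.

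- **Section 2.2.1, secondary outcomes.** Healthcare usage is taken from an investigator-created logbook by "measuring the number of hospital visits or GP visits for cardiovascular conditions during the phone calls".
- **Table 3, W2 session.** The nurse's tasks include: "Instruct patients to report any healthcare usage during the intervention to maintain accurate monitoring". The W3 and W4 rows repeat the week 2 content by reference.
- **Section 2.2.1, primary outcomes.** Safety covers "discomfort or adverse effects related to NGPS intervention by keeping a daily logbook and reporting via telephone or face-to-face".
- **Section 2.2.2.** The reporting rule for harms is: "Any adverse events related to physical activity, such as musculoskeletal aches and pain, dizziness, and falls, will be presented as the absolute number of events", together with a percentage.
- **Section 1, objective 3.** Healthcare usage is listed under an aim that begins "To test the preliminary effects of the NGPS intervention on cardiovascular health outcomes".

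**The concern.** The usage outcome is filtered by cause: only cardiovascular visits count. The instruction to patients has no such filter. The same calls could therefore give a cardiovascular-only count or an all-cause count, depending on which text the person holding the logbook follows.

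This also touches safety, which is a primary outcome. The safety definition has a different filter, relatedness. When one record is filtered by cause and the other by attribution, some visits can pass through both. The participants have heart failure, coronary disease, stroke, arrhythmia and similar conditions, and there is no control group. Whether a given admission has anything to do with the programme is hard to decide at the time. An all-cause record with reasons is what lets that judgement be checked later.

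**Working it through.** No arithmetic bears on this point. The only sample-size figure reproduces: 12 / (1 − 0.20) = 15 recruited. Nothing below changes it. The check is a reading of the passages side by side.

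**Step 1: scope of usage.** Section 2.2.1 counts hospital or GP visits with a cardiovascular cause. Table 3 asks for usage of any kind during the intervention. The two can operate together if the broad wording governs collection and the narrow wording governs counting, but the article does not say so.

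**Step 2: scope of safety.** Section 2.2.1 has no cardiovascular filter but requires a relation to the intervention. The reporting sentence in section 2.2.2 is narrower and requires a relation to physical activity. Neither says that a hospital or GP visit arising from a harm is recorded as such.

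**Step 3: cross the two filters.** Taking the wording literally, each visit falls into one of four cells:

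| Visit | Event judged related | Event judged unrelated |
|---|---|---|
| Non-cardiovascular | Event in safety; visit not in usage | In neither reported outcome |
| Cardiovascular | In safety and in usage | In secondary usage only |

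**Step 4: place the named harms.** A fall or musculoskeletal pain arising from the activity programme sits in the upper left cell. It is counted as an adverse event whether or not it led to a visit. Only the visit as a usage item is uncounted. Dizziness related to physical activity is also counted as an adverse event, however any resulting visit is classified.

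**Step 5: find the gap.** The right-hand column is what remains. The upper cell has no reported home. The lower cell is reported, but no sentence brings it to safety review. Which column a visit falls in depends on an attribution made without a comparison group, in patients with background cardiovascular disease.

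**The case against.** The strongest reply is that harms already have a separate route. Safety is a primary outcome with a daily logbook and telephone or face-to-face reporting, and a secondary usage measure need not double as safety surveillance. A cardiovascular-only usage count also fits objective 3. Both points stand, and the fix below leaves that outcome as it is.

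The second reply is that Table 3 says what patients report and section 2.2.1 says what is counted, so there is no conflict. That is a workable reading, but the article does not state it.

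The third is that Table 3 is labelled preliminary and will be revised (section 2.1.7), that standard operating procedures are promised (section 2.2.3), and that an article condenses the full protocol. This is fair for the mechanics of passing entries between logs, and it lowers the weight of the point. It does not remove the relatedness limits, which the article states, or the difference in scope between two passages that are both in print.

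A reader might infer more than the text supports:

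- **That visits for the harms the plan names leave those harms uncounted.** They do not: sections 2.2.1 and 2.2.2 count the harms as adverse events when related.
- **That every non-cardiovascular visit is lost.** Under Table 3, patients are asked to tell the nurse about such visits. It is the outcome count that excludes them.
- **That week 1, or 1 of 4 intervention weeks (25%), is missed because the instruction first appears in W2.** The W2 wording refers to the whole intervention, so it can prompt recall of week 1, and no week 2 start is given for the daily safety logbook. The 25% is a share of weeks, not of data.

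**Conclusion.** The concern holds in a limited form. The scopes in section 2.2.1 and Table 3 differ and should be reconciled. Because the safety outcome is limited to related events, a non-cardiovascular visit judged unrelated is reported nowhere, and a cardiovascular admission judged unrelated is reported only as secondary usage.

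The size is minor. The usage outcome is secondary and exploratory, the pilot is descriptive, and no stated figure moves. For scale only, one participant is 1/15 = 6.7% of those recruited; this is the weight of a single case, not an expected loss. The documents give no event rate from which to estimate one.

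The conclusion assumes that the relatedness wording is applied as written when events are entered and reported, and that no fuller procedure captures all visits regardless of cause. If the full protocol or the operating procedures already do that, only the wording needs aligning.

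**What to change.** In section 2.2.1, state that all unplanned hospital and GP visits are recorded with date and reason, which Table 3 already asks patients to report. Keep the cardiovascular subset as the stated secondary outcome. Add that each unplanned visit is entered in the safety record and reviewed as a possible adverse event, whatever its presumed cause. Use the same wording in Table 3. Placing the instruction in the W1 self-management session is optional, but would give one rule from the start.

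The cost is a few sentences and one extra logbook field, since the contacts already take place. The downside is slightly more data to review and possibly a less favourable safety count.
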